**ABSTRACT**

**BACKGROUND** Approximately 11,000 Veterans present to a VAMC annually with an acute ischemic stroke or TIA. The cornerstone of secondary stroke/TIA prevention includes delivering timely, guideline-concordant vascular risk factor management. Over the past decade, obstructive sleep apnea (OSA) has been recognized as a potent, underdiagnosed, and inadequately treated cerebrovascular risk factor. OSA is very common among patients with stroke/TIA with a prevalence of 70-80%. Despite being highly prevalent, 70-80% of patients with OSA are neither diagnosed nor treated. Untreated OSA has been associated with poor outcomes among patients with cerebrovascular disease including higher mortality and worse functional status. The mainstay of OSA therapy is positive airway pressure (PAP). PAP reduces recurrent vascular events, improves neurological symptoms and functional status among stroke/TIA patients with OSA. The evidence favoring neurological recovery is strongest when interventions are applied early post-stroke/TIA. Guidelines recommend diagnosing and treating OSA for eligible stroke and TIA patients; however, within VHA, very few stroke or TIA patients receive OSA screening. This guideline recommendation was informed in part by clinical trials utilizing an acute OSA assessment protocol developed and implemented by our group.

**OBJECTIVES:** Utilizing a Hybrid Type I, randomized, stepped-wedge trial at 6 diverse VAMCs, to implement and evaluate the effectiveness and sustainability of implementation strategies utilized in an Addressing Sleep Apnea Post-stroke (ASAP) quality improvement program designed to improve facility-level diagnosis and management of OSA.

**METHODOLOGY:** We will initiate the ASAP program at 6 VAMCs that annually care for at least 50 Veterans admitted with a stroke but without a known history of OSA for a twenty-one-month intervention period followed by a sustainability period at 4 of the 6

participating sites. Effectiveness of the intervention will be measured across one primary effectiveness outcome (30-day facility-level diagnostic rate) and three secondary domains (30-day treatment rate, 90-day recurrent vascular event rate, and 90-day all-cause readmission rate). The ASAP quality improvement intervention will include a systems redesign virtual collaborative and data monitoring; implementation strategies will include external facilitation and audit and feedback. The Consolidated Framework for Implementation Research (CFIR) will be used to evaluate the implementation of the intervention and of the implementation strategies at several discrete time points during ASAP: (1) baseline; (2) active implementation, (7 Months, 14 Months, and 21 months, which marks the end of active implementation); and (3) at the end of the sustainability period. GO Scores and CFIR construct scoring will be completed for Wave 1 and Wave 2 sites across these time points. CFIR and GO Scores for Wave 3 sites will not include sustainability assessments; given COVID-related changes to the project timeline, Wave 3 sites do not have a sustainability period. The primary implementation outcome will be obtaining a GO score of 6 or more by the end of active implementation. The secondary implementation outcome will be a positive change in GO score of 4 or more by the end of active implementation. We will construct a business case analysis at the facility-level, including financial components related to the intervention. We believe that we can implement a sustainable ASAP program across diverse VAMCs which: (1) improves OSA diagnosis, treatment, and 90-day recurrent vascular event rate, and; (2) has a business case favoring intervention sites with the highest baseline recurrent vascular event rate.

**CLINICAL RELATIONSHIPS:** Interventions that improve diagnosis and management of OSA among Veterans with stroke/TIA are necessary to improve outcomes; implementation science strategies can assess the uptake and sustainability of this intervention. Because the intervention and implementation strategies have been designed using existing VHA infrastructure, if effective, the program would be ready for scaling system wide. Results from the business-case analysis for ASAP will be shared with VAMC providers and local leadership who may be interested in implementing this program at their facility. Additionally, an acute sleep service could be adapted to other patient populations (e.g., chronic obstructive pulmonary disease), both within and outside of VHA.

### **List of Abbreviations**

|         |                                                        |
|---------|--------------------------------------------------------|
| ACS     | Acute Coronary Syndrome                                |
| AHA/ASA | American Heart Association/American Stroke Association |
| ASAP    | Addressing Sleep Apnea Post-stroke/TIA                 |
| BS      | Bachelor of Science                                    |

|       |                                                           |
|-------|-----------------------------------------------------------|
| CCSH  | Certificate in Clinical Sleep Health                      |
| CDW   | Corporate Data Warehouse                                  |
| CHERP | Center for Health Equity Research and Promotion           |
| CAN   | Coincidence Analysis                                      |
| CCMs  | Configurational Comparative Methods                       |
| CHF   | Congestive Heart Failure                                  |
| CFIR  | Consolidated Framework for Implementation Research (CFIR) |
| COVID | Corona virus disease                                      |
| CPAP  | Continuous Positive Air Pressure                          |
| DMAIC | Define, Measure, Analyze, Improve, and Control            |
| DO    | Doctor of Osteopathic Medicine                            |
| DSS   | Decision Support System                                   |
| CHAMP | CHampion Measure of Performance                           |
| FMEA  | Failure Modes and Effects Analysis                        |
| FTE   | Full Time Equivalent                                      |
| GO    | Group Organizational                                      |
| HIPAA | Health Insurance Portability and Accountability Act       |
| HST   | Home Sleep Test                                           |
| ICD   | International Classification of Diseases                  |
| IOP   | Intraoperative Platform                                   |
| IRB   | Institutional Review Board                                |
| LSI   | Local Site Investigator                                   |
| MBA   | Master of Business Administration                         |
| MS    | Master of Science                                         |
| MSEd  | Master of Science in Education                            |

|        |                                                        |
|--------|--------------------------------------------------------|
| MD     | Medical Degree                                         |
| MIT    | Medical Instrument Technician                          |
| MI     | Myocardial Infarction                                  |
| NP     | Nurse Practitioner                                     |
| OSA    | Obstructive Sleep Apnea                                |
| ORCA   | Organizational Readiness to Change Assessment          |
| PAP    | Positive Airway Pressure                               |
| PDSA   | Plan, Do, Study, Act                                   |
| PhD    | Doctor of Philosophy                                   |
| PRIS-M | Precision Monitoring to Transform Care                 |
| PRIUS  | Prospectively-Reported Implementation Update and Score |
| PSAT   | Program Sustainability Assessment Tool                 |
| PSG    | Polysomnography                                        |
| QUERI  | Quality Evaluation Research Initiative                 |
| QI     | Quality Improvement                                    |
| R&D    | Research and Development                               |
| REDCap | Research Electronic Data Capture                       |
| RPIW   | Rapid Process Improvement Workshop                     |
| RPSGT  | Registered Polysomnographic Technologist               |
| RST    | Respiratory Sleep Technologist                         |
| TIA    | Transient Ischemic Attack                              |
| VA     | Veterans Affairs                                       |
| VAMC   | Veterans Affairs Medical Center                        |
| VHA    | Veterans Affairs Healthcare                            |
| VSSC   | VHA Support Service Center                             |

## Addressing Sleep Apnea Post-stroke (ASAP) multisite research project

### 1. Introduction

Approximately 11,000 Veterans present to a VAMC annually with an acute ischemic stroke or TIA. The cornerstone of secondary stroke/TIA prevention includes delivering timely, guideline-concordant vascular risk factor management. Over the past decade, OSA has been recognized as a potent, underdiagnosed, and inadequately treated cerebrovascular risk factor. OSA is very common among patients with stroke/TIA with a prevalence of 70-80%. Despite being highly prevalent, 70-80% of patients with OSA are neither diagnosed nor treated. History, physical examination, and screening instruments (e.g., Berlin Questionnaire) are inaccurate among patients with cerebrovascular disease. Given that no combination of symptoms or physical examination findings has adequate sensitivity or specificity for the diagnosis of OSA post-stroke/TIA, only PSG or auto-PAP (used diagnostically) can identify disease status post-cerebrovascular event. Recognizing these concerns, the AHA/ASA guidelines recommend that a sleep study (as opposed to screening questionnaires) should be used to identify the presence or absence of OSA among eligible patients with acute ischemic stroke or TIA.

The American Academy of Sleep Medicine (AASM) recommends PSG either conducted in a sleep laboratory (the gold standard) or unattended PSG conducted in patients' homes for the detection of OSA. Unfortunately, there are several barriers to the use of PSG. Within the VHA there are long wait times for scheduling PSG (within or outside of the VHA). Veterans in rural areas often must travel great distances to the nearest sleep laboratory. An alternative to PSG in a sleep laboratory is unattended PSG. Studies have reported good agreement between unattended PSG and formal PSG (sensitivities: 75-100%; specificities: 87-100%). The VHA Sleep-Related Breathing Disorders Source Book states that alternatives to full PSG may be acceptable when patients cannot be assessed with PSG in a sleep laboratory. Other alternative approaches include the use of auto-PAP. Several studies have evaluated the use of auto-PAP devices used diagnostically, finding them to have acceptable validity among stroke/TIA patients.

Untreated OSA has been associated with poor outcomes among patients with cerebrovascular disease including higher mortality and worse functional status. The mainstay of OSA therapy is PAP. The literature demonstrating the benefits of PAP among the general population with OSA is extensive. PAP therapy dramatically reduces or eliminates sleep-related breathing perturbations and improves a variety of outcomes including daytime sleepiness, cognition, quality of life and hypertension control. Beyond these general benefits of PAP therapy for OSA, randomized clinical trials and observational cohort studies have demonstrated the effectiveness of PAP in improving neurological and functional outcomes post-stroke/TIA. Several randomized trials evaluated the use of early PAP in the acute stroke period. These acute stroke

studies have demonstrated improvements in neurologic symptoms with PAP therapy that are equivalent to those observed with tPA therapy. One randomized trial evaluated the use of early PAP among acute TIA patients found that the vascular event rate decreased as PAP use increased: 8% for no PAP use; 6% for some PAP use; and 0% for good PAP use. Four randomized controlled trials evaluated PAP in subacute stroke patients. The largest of the cohort studies (N=189) reported that patients  $\geq 2$  months post-stroke with OSA who did not use PAP had much higher recurrent stroke rates than patients who used PAP (32% vs 14%,  $p=0.02$ ) and higher adjusted incidence of nonfatal vascular events (HR 2.87 [1.11- 7.71]). The number-needed-to-treat to prevent one new vascular event was 4.9 patients. A recent meta-analysis of ten randomized controlled trials among patients with ischemic stroke identified a relationship between neurological symptom improvement and PAP adherence. A study of patients  $\geq 6$  weeks after an index stroke found that PAP users had a recurrent vascular event rate of 3% compared with 15% in PAP non-users. These data demonstrate that recurrent event reduction occurs when treatment is provided early and when patients adhere to PAP.

In short, PAP reduces recurrent vascular events, improves neurological symptoms and functional status among stroke/TIA patients with OSA. The evidence favoring neurological recovery is strongest when interventions are applied early post-stroke/TIA. Guidelines recommend diagnosing and treating OSA for eligible stroke and TIA patients; however, within VHA, very few stroke or TIA patients receive OSA screening. This guideline recommendation was informed in part by clinical trials utilizing an acute OSA assessment protocol developed and implemented by our group. To address the observed gap in care, we propose a Hybrid Type I, randomized, stepped-wedge trial to increase the rate of timely, guideline-concordant diagnosis and treatment of OSA among Veterans with ischemic stroke/TIA and thereby reduce recurrent vascular events.

## 2. Objectives

Utilizing a Hybrid Type I, randomized, stepped-wedge trial at 6 diverse VAMCs as intervention sites and 30 usual care control sites, to implement and evaluate the effectiveness and sustainability of implementation strategies utilized in an Addressing Sleep Apnea Post-stroke (ASAP) program designed to improve facility-level diagnosis and management of OSA. These objectives will be accomplished through the following specific aims:

**Specific Aim 1:** Evaluate the effectiveness of an intervention for the early diagnosis and treatment of OSA among Veterans with ischemic stroke and TIA. The intervention program will include a systems redesign Virtual Collaborative and data monitoring. ASAP includes external facilitation and audit and feedback as implementation strategies, which will be assessed during the intervention period. Sites will locally-tailor and implement an Addressing Sleep Apnea Post-stroke (ASAP) quality improvement program. The sites will choose a diagnostic strategy (i.e., unattended polysomnography [PSG]/home sleep test [HST], in-laboratory PSG, direct to auto-titrating [auto]-PAP) and a therapeutic strategy (e.g., in-laboratory PAP titration, auto-PAP). The primary effectiveness outcome, evaluated at the facility-level, will be the 30-day sleep apnea diagnostic rate. The three secondary effectiveness outcomes will be 1. the 30-day

treatment rate, 2. the 90-day recurrent vascular event rate and 3. the 90-day all-cause readmission rate. We hypothesize that the: mean facility diagnostic rate (PSG within 30 days of presentation) will be 70% for eligible patients during intervention periods vs 7% for controls; the mean facility treatment rate (PAP initiation within 30 days of presentation) will be 50% for intervention vs 2% for controls; mean facility 90-day recurrent vascular event rate (stroke, MI/acute coronary syndrome [ACS], congestive heart failure [CHF] and all-cause mortality) will be 3.5% for intervention vs 10% for controls; and; mean facility 90-day all-cause readmission rate will be 20% for intervention vs 33% for controls. Chart review and administrative data will be used to ascertain outcomes.

**Specific Aim 2:** Evaluate the implementation of the intervention program. This implementation evaluation will be grounded in the Consolidated Framework for Implementation Research (CFIR) and examine how implementation strategies and features of local context combine and interact to influence the implementation of ASAP across six diverse VAMCs. We hypothesize that this project will contribute generalizable knowledge to implementation science through detailed specification and evaluation of each implementation strategy, in-depth characterization of local context at the six facilities, and rigorous qualitative and mixed-methods analyses to examine how implementation strategies and features of local context influence outcomes. Furthermore, we hypothesize that contextual factors will be associated with our implementation outcomes, both primary (i.e., obtaining a GO score of 6 or more by the end of active implementation) and secondary (i.e., a positive change in GO score of 4 or more by the end of active implementation). The analyses leading to these findings will focus both within and across facilities, with special attention to facility- and patient-level factors contributing to implementation success. CFIR constructs will be applied to de-identified interview data.

**Specific Aim 3:** Evaluate the sustainability of the intervention. Sustainability will be evaluated immediately following the 21-month active implementation period and will be of variable duration based on WAVE randomization (WAVE 1 and 2 sites will have each have a 7-month sustainability period whereas WAVE 3 will not have a sustainability period). The primary sustainability outcome at WAVE 1 and 2 sites will include the number of patients who receive diagnosis within 30 days of presentation. We hypothesize that sustainability will be greatest at sites that use HST as their primary diagnostic approach and have champions who continue to engage with systems redesign.

**Specific Aim 4:** Perform a business-case analysis. We will construct a business-case analysis at the facility-level and will include financial components related to the intervention. We hypothesize that the business-case analysis will favor the intervention at sites with the highest baseline recurrent vascular event rate.

The significance of the proposed ASAP project to the VHA is grounded in both the high prevalence of OSA among Veterans and the low baseline rates of guideline concordant OSA screening post-stroke/TIA. This proposal addresses two major barriers in the implementation of the AHA/ASA OSA screening guideline: lack of a study powered to detect differences in recurrent vascular events and lack of a business-case analysis to support adoption of the AHA/ASA recommendation. If the project improves screening

and treatment of OSA, then it is likely that the Veteran population will realize significant improvements in clinical outcomes. The planned implementation evaluation and sustainability assessment will provide insights that are likely to be relevant to other quality improvement (QI) activities. The ASAP proposal advances the priorities of our partners within VA Patient Care Services (Drs. [name], [name], and [name]). Moreover, the evaluation of an “acute sleep service” is an innovative approach that is generalizable both within and outside VHA. The intervention and implementation strategies have been designed using existing VHA infrastructure, so if the intervention is effective, then the program will be ready for scaling system wide.

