**30-day Treatment Rate** is defined as PAP treatment initiation within 30 days of presentation to the facility. The mean facility 30-day treatment rate is defined as PAP initiation within 30 days of admission. For this outcome, the denominator will be patients who are newly diagnosed with OSA. Patients with a prior diagnosis of sleep apnea (regardless of CPAP usage) and those who die within 7 days of discharge will be excluded. Patients who have a new diagnosis of central sleep apnea or Cheyne stokes (within 30-days of admission) or who are using Adaptive Servo Ventilation (ASV) are excluded. There may be no (or very few) patients in the baseline phase with OSA who are given treatment. Therefore, we will collapse data across all control time increments and all intervention time increments for each site.

**90-day Recurrent Vascular Event Rate** includes an ED or hospital admission for any of the following: TIA, stroke, myocardial infarction (MI), acute coronary syndrome (ACS), arrhythmia, congestive heart failure (CHF), and all-cause mortality. The recurrent vascular event rate is measured from the day discharge.

Patients who are transferred out from the index stay are excluded. We expect the intervention only to reduce recurrent vascular events among patients with OSA who receive and adhere to treatment.

**90-day All-Cause Readmission Rate** includes an inpatient admission for any cause at either a VA or non-VA acute care facility. Planned readmissions are not included in the numerator. Patients who are transferred out from the index stay are excluded from the denominator. Exclude patients who were transferred to an acute care facility at any time during the index admission. As with the recurrent vascular event rate, we expect the intervention only to reduce readmission among patients who are diagnosed with OSA who receive and adhere to treatment.

**Baseline Characteristics** We expect that the characteristics of the stroke/TIA patients will remain relatively constant at each site across the different time points. We will summarize patient characteristics (e.g., demographics) by site and time. Any differences will be considered when interpreting results of analyses.

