## **Analysis of the Primary Effectiveness Outcome**

### **Diagnostic Rate Analysis**

A generalized linear mixed model will be fit to the patient-level outcome of diagnostic testing (yes/no) to conduct facility-level inference. The primary effect of interest is the effect of the intervention during active implementation versus baseline. Control sites are included to add accuracy in estimation of the secular time trend. A non-exact match approach is planned for this analysis (i.e., unconditional) since this model is being fit to patient-level data which will be used to conduct facility-level inference and there is no guarantee that patients in control sites that were loosely matched to an intervention site using facility factors are similar. This approach will use all available control site data without pairing specific control sites to each ASAP site. Effects in the model include a site-level indicator of intervention site vs control site, indicator for each site and data period corresponding to active implementation or sustainability phase, and time (as categorical, indicating each 7-month data period). The model will also include a random intercept for site to account for potential correlation among patients from the same site. Our interest is in testing the effect of the ASAP intervention on the proportion of patients who are diagnosed at the site-level. This model will also be fit adjusting for any important patient covariates (i.e., stroke severity). Both unadjusted and adjusted results will be reported. Contrasts from the model will also be estimated. All statistical tests will be two-sided, with p-values < 0.05 considered statistically significant. All analyses will include checking of assumptions and model fit.

**Analysis of Secondary Outcomes** As described above, because the treatment rate can only be assessed among the patients who have been diagnosed, we will be limited in our analysis of treatment. If several patients are diagnosed in the during the control phase (which is unlikely), we would use the same mixed model approach as with other outcomes. However, because we expect to have very

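### The 30-day treatment rate runs its clock from presentation but divides by newly diagnosed patients, with no limit on when they are diagnosed, so it can rise with no change in care after a positive test

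*Protocol*

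**What the plan says.** Section 2, Specific Aim 1 of the Protocol gives the hypothesis and the clock: "the mean facility treatment rate (PAP initiation within 30 days of presentation) will be 50% for intervention vs 2% for controls". It names no denominator.

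The definition is in section 5.7.c, under 30-day Treatment Rate. The outcome "is defined as PAP treatment initiation within 30 days of presentation to the facility", and the next sentence changes the start: "The mean facility 30-day treatment rate is defined as PAP initiation within 30 days of admission". The denominator follows: "For this outcome, the denominator will be patients who are newly diagnosed with OSA". No window is put on that diagnosis, although the central-apnoea exclusion in the same paragraph is limited to 30 days from admission. Analysis of Secondary Outcomes confirms the restriction: "the treatment rate can only be assessed among the patients who have been diagnosed".

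Testing itself is expected to change greatly between phases. Specific Aim 1 hypothesises that the "mean facility diagnostic rate (PSG within 30 days of presentation) will be 70% for eligible patients during intervention periods vs 7% for controls". Section 1 describes the usual-care starting point: "Within the VHA there are long wait times for scheduling PSG (within or outside of the VHA").

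Baseline and active-implementation data are each to be collapsed within site and compared by a within-site permutation test, with Fisher's exact test on the pooled patients as an addition.

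**The concern.** The numerator counts from presentation. The denominator is formed later, by an event that the intervention is designed to bring about. Two things then differ between phases for reasons unrelated to treatment of a diagnosed patient:

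- **Who is counted.** Read literally, a patient first diagnosed on day 45 is in the denominator and cannot be a success. Such patients should make up a larger share of diagnoses in the baseline phase than under the programme.
- **How much time is left.** Even if the diagnosis must fall within 30 days, a patient tested on day 2 has 28 days to start PAP and one tested on day 27 has 3.

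Both push towards the intervention whenever the programme brings testing forward. The shift would tend to have the same sign at all six sites. A permutation test on the mean within-site difference reaches its smallest two-sided p-value, 2/64 = 0.031, whenever all six differences agree in sign, however small they are. A result could thus be reported as better treatment of diagnosed OSA when only testing had changed.

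**Working it through.** **Inputs from the Protocol.** Tested by day 30: 7% control, 70% intervention (section 2). OSA prevalence 70-80% (section 1). About 64 patients per site per 7-month period, from 111 × 7/12 = 64.75 (section 5.7.c). Hypothesised treatment rate 50% versus 2%.

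**Assumptions, not in the Protocol.** Time to test is exponential. The lag from test to PAP is exponential with median 7, 14 or 21 days. 80% of those diagnosed ever start PAP. Lag and uptake are identical in both phases.

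**1. The plan's own figure.** No formula or power calculation accompanies 50% versus 2%, so it cannot be reproduced, only checked for consistency. Newly diagnosed patients as a share of all eligible:

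- Active: 0.70 × 0.70 = 49% to 0.70 × 0.80 = 56%
- Control: 0.07 × 0.70 = 4.9% to 0.07 × 0.80 = 5.6%

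If 50% versus 2% refers to all eligible patients, PAP uptake among the diagnosed is 0.50/0.56 = 89% to 0.50/0.49 = 102% (active) and 0.02/0.056 = 36% to 0.02/0.049 = 41% (control). If it refers to the newly diagnosed, the all-eligible rates are 0.50 × 0.49 = 24.5% to 0.50 × 0.56 = 28% and 0.02 × 0.049 = 0.10% to 0.02 × 0.056 = 0.11%. The active 50% lies almost exactly at the share expected to be newly diagnosed, which suggests an all-eligible denominator but does not prove it.

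**2. Time left after the test.** With median lag m and every patient eventually starting, P(PAP by day 30 | test on day d) = 1 − 2^(−(30−d)/m). For m = 14, a test on day 3 gives 73.7% and a test on day 25 gives 21.9%.

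**3. Effect of timing on the phase comparison.** Let λ = −ln(1 − F)/30, with F = 0.07 or 0.70, so λ = 0.00242 or 0.0401 per day. Let μ = ln 2/m, and let W be the last day on which a diagnosis counts. Then

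rate = 0.80 × P(T + L ≤ 30)/P(T ≤ W),

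where P(T + L ≤ 30) = 1 − (μe^(−30λ) − λe^(−30μ))/(μ − λ) and P(T ≤ W) = 1 − e^(−λW).

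Example, m = 7 (μ = 0.0990) and W = 90: control 0.80 × 0.0480/0.1956 = 19.6%; active 0.80 × 0.5305/0.9730 = 43.6%.

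The table comes from a simulation of 1,000,000 OSA patients per phase; the formula agrees to within 0.2 points. Entries are control versus active.

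| Median lag | Diagnosis ≤ 30 days | Diagnosis ≤ 90 days | Diagnosis ≤ 365 days |
|---|---|---|---|
| Near zero | 80.1% vs 80.0% | 28.6% vs 57.6% | 9.5% vs 56.1% |
| 7 days | 54.7% vs 60.6% | 19.6% vs 43.7% | 6.5% vs 42.4% |
| 14 days | 38.7% vs 44.0% | 13.9% vs 31.7% | 4.6% vs 30.9% |
| 21 days | 29.7% vs 34.0% | 10.6% vs 24.5% | 3.5% vs 23.7% |

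With a 30-day window and lags of 7, 14 and 21 days the differences are 5.9, 5.3 and 4.3 points. With a near-zero lag the gap vanishes under the 30-day window but not under the wider ones. These figures isolate timing: the simulated patients are the same in both phases, so any difference in which kind of patient gets tested comes on top and is not quantified.

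**4. Size of the denominators.** Newly diagnosed per site-period: 64.75 × 0.049 = 3.2 to 64.75 × 0.056 = 3.6 in control, against 64.75 × 0.49 = 32 to 64.75 × 0.56 = 36 in active implementation. Collapsing periods addresses this sparsity but not the mismatch.

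**The case against.** The strongest defence is that the clock is intended. Aim 1 is about early diagnosis and treatment, and section 1 ties benefit to early PAP. If diagnosed patients reach PAP sooner after the stroke because they were tested sooner, that is a real programme effect, and the Protocol nowhere says that this outcome isolates care after a positive test. This stands as a defence of the presentation clock. It does not defend pairing that clock with a denominator that the intervention itself forms.

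Secondly, a 30-day diagnosis window is the more coherent reading: the outcome carries 30 days in its name, the diagnostic rate is defined at 30 days, and an SAP that is not shown may state the window. That is fair, and it would remove the largest figures above. It would still leave unequal time to start PAP and a group selected by testing.

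Thirdly, sites may go directly to auto-PAP, where test and treatment can coincide. There the artefact is nil under a 30-day window, but this is one option on the menu.

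Finally, the sentence in Aim 1 gives no denominator, and on an all-eligible denominator the problem disappears. That is correct. The fault lies in the definition in section 5.7.c, and the two sections need to be brought together.

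**Conclusion.** The point holds as a definitional fault in a named secondary effectiveness outcome; the primary outcome is unaffected. Under the assumptions stated, timing alone moves the rate by about 4 to 6 points towards the intervention if diagnosis must fall within 30 days and the median lag is 7 to 21 days, by nothing if PAP starts at the test, and by about 14 to 24 points at those lags with a 90-day window. The Protocol fixes neither the lag nor the window, so no single figure can be given.

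Three stronger readings are tempting but not supported:

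- **A shift of 21 to 27 points even with a 30-day window.** This follows if usual-care tests are spread evenly over days 0-30 and programme tests over days 0-5 (77% versus 98%, 68% versus 94% and 59% versus 86% for mean lags of 7, 10 and 14 days). The Protocol gives no such test-day distributions. Long scheduling waits would place usual-care patients outside the 30 days rather than late within them.
- **The outcome merely repeats the primary.** The primary is a yes/no at 30 days and scores a test on day 2 and one on day 27 alike, so it does not measure speed within the window.
- **Any rise is an artefact.** Earlier PAP is a stated aim. What cannot be concluded is that diagnosed patients were treated better.

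**What to change.** In section 5.7.c, 30-day Treatment Rate:

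1. Use one clock start, presentation, and delete the alternative wording that counts from admission.
2. Make the main 30-day treatment rate PAP initiation within 30 days of presentation among all eligible patients, the denominator that section 5.2.a gives for the diagnostic rate. This fits Aim 1 and allows the primary outcome's mixed model to be considered in place of the collapsed comparison.
3. Keep the rate among the newly diagnosed as a descriptive supplement, limited to OSA diagnosed within 30 days of presentation. Report times from presentation to test and from test to PAP by phase, and state that this rate is not to be read as an intervention effect on treatment after diagnosis.
4. Reconcile the 50% versus 2% in section 2 with the chosen denominator.

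Moving the clock to the positive test as the main outcome is not recommended: it departs from the aim of early post-stroke treatment and still conditions on diagnosis.

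The cost is outcome wording and reprogramming. Applying a 30-day rule to testing and to PAP already requires both dates. The drawback is that the all-eligible rate combines testing and treatment and so does not isolate care after diagnosis; the supplement describes that part without testing it.
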